### Secondary study parameters

Angiographic success will be defined as dissolution of >95% of the thrombus with outflow to at least one crural artery. Clinical change/success will be reported according to Rutherford’s recommended scale for gauging changes in clinical status (table 1). Amputations will be defined as either major (above or below knee amputation) or minor (metatarsal or toe amputation). Additional interventions will be categorised as either surgical (eg, thromboembolectomy, bypass graft surgery) or percutaneous (percutaneous transluminal angioplasty, stent placement) and as either required for restoration of patency or necessary for correction of underlying lesions. We will also determine microcirculation of the limb (by Laser Doppler measurements, Perimed Instruments, Järfälla, Sweden), 30-day mortality, conversion to surgery, serum fibrinogen concentrations measured during thrombolytic treatment on a daily basis, pain by visual analogue scale (VAS) and quality of life by SF-36 questionnaires. The duration of thrombolysis will be defined by the time span between initiation and completion angiography.

**Table 1 T1:** Rutherford’s^24^ recommended scale for gauging changes in clinical status

+3	Markedly improved: no ischaemic symptoms and any foot lesions completely healed; ABI essentially ‘normalised’ (increased to >0.90)
+2	Moderately improved: no open foot lesions; still symptomatic but only with exercise and improved by at least one clinical chronic ischaemia category; ABI not normalised but increased by >0.10
+1	Minimally improved: >0.10 increase in ABI* but no categorical improvement or vice versa (ie, upward categorical shift without an increase in ABI of >0.10)
0	No change: no categorical shift and <0.10 change in ABI
−1	Mildly worse: no categorical shift but ABI decreased >0.10 or downward categorical shift with ABI decrease <0.10
−2	Moderately worse: one category worse or unexpected minor amputation
−3	Markedly worse: more than one category worse or unexpected major amputations

*In cases where the ABI cannot be accurately measured, an index based on the toe pressure, or any measurable pressure distal to the site of revascularisation, may be substituted.

ABI, Ankle Brachial Index.

Adapted from Rutherford RB et al. JVS 1997.

### Patients and eligibility criteria

The present feasibility and safety study is a non-randomised phase II trial to be conducted in our university hospital in Amsterdam, the Netherlands. Usually, in a phase II trial 10–20 patients are investigated to confirm an occurrence of toxic effects or SAEs<20%. We chose a sample size of 20 to assess the safety of the investigational treatment. Eligibility criteria are listed in table 2. Inclusion of 20 eligible patient is expected within 1.5 years. Written informed consent will be acquired by a member of the Research Team after information about the study has been provided by the treating doctor.

**Table 2 T2:** Eligibility criteria

Inclusion criteria	Men and women older than 18 and younger than 85 years Patients with a maximum of 2 weeks of symptoms for lower limb ischaemia due to thrombosed/occluded iliofemoral, femoropopliteal or femorocrural native arteries or iliofemoral, femoropopliteal or femorocrural venous or prosthetic bypass grafts Patients appropriate for thrombolysis, that is, with acute lower limb ischaemia class I and IIa according to the Rutherford classification Patients who understand the nature of the procedure and provide written informed consent before enrolment in the study
Exclusion criteria	Patients with clinical complaints of acute lower limb ischaemia due to thrombosis of iliofemoral, femoropopliteal or femorocrural native arteries, or iliofemoral, femoropopliteal or femorocrural venous or prosthetic bypass grafts for >2 weeks Patients with thrombosed popliteal aneurysms Patients with absolute contraindications for administration of antiplatelet therapy, anticoagulants or thrombolytics History of recent (<6 weeks) ischaemic stroke, cerebral haemorrhagic or myocardial infarction Patients with recent (<6 weeks) surgery Severe hypertension (diastolic blood pressure >110 mm Hg and/or systolic blood pressure >200 mm Hg) Current malignancy or severe comorbid condition with a life expectancy of <6 months Patients with uncorrected bleeding disorders (gastrointestinal ulcer, menorrhagia, liver failure) Women with childbearing potential not taking adequate contraceptives or currently breast feeding Pregnancy Patients who are currently participating in another investigational drug or device study Patients younger than 18 years or older than 85 years Patients with contraindications for Luminity microbubbles, that is: Hypersensitivity to perflutren or to any of the components of Luminity Recent acute coronary syndrome or clinically unstable ischaemic cardiac disease, including evolving or ongoing myocardial infarction, unstable angina at rest within the last seven days, significant worsening of cardiac symptoms within the last seven days, recent coronary artery intervention or other factors suggesting clinical instability (eg, recent deterioration of ECG, laboratory or clinical findings), acute cardiac failure, class III/IV cardiac failure or severe rhythm disorders Patients known to have right-to-left cardiac shunts, severe pulmonary hypertension (pulmonary artery pressure>90 mm Hg), uncontrolled systemic hypertension and in patients with Global Initiative for Obstructive Lung Disease (GOLD) stage IV chronic obstructive pulmonary disease, diffuse interstitial fibrosis or adult respiratory distress syndrome Patients with cardiovascular instability where dobutamine is contraindicated

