## Introduction

Acute limb ischaemia can be caused by a thrombus occluding an artery in an arm or leg. This is an emergency situation that can result in amputation or death if not treated successfully.^1^ Intra-arterial infusion of thrombolytic agents, that is, catheter-directed thrombolysis, can restore blood flow by dissolving the clot, as a less invasive alternative to surgical thromboembolectomy.^2^ In comparison with the lysis of small arterial occlusions in patients with myocardial infarction, larger peripheral arterial occlusions require higher doses of lytic agents and infusion over a longer period of time. Inevitably, such treatment is accompanied by a risk of major haemorrhagic complications, such as haemorrhagic stroke, in up to 8% of patients.^3^ Furthermore, this technique is time-consuming (several days of bed rest is usually required) and repeated angiography for treatment monitoring is needed, putting patients at risk for contrast-induced nephropathy. As a result, this leads to high morbidity rates and a significant patient burden. Methods to improve this therapy are therefore highly sought after.

A potential accelerator of thrombolytic therapy is contrast-enhanced ultrasound. Contrast agents, consisting of 5–10 µm gas-filled particles (microbubbles), have initially been used as diagnostic ultrasound contrast enhancers. A new field of research investigates these agents for potential therapeutic purposes such as targeted drug delivery and thrombolysis.^4^ The proposed mechanism of action in thrombolysis is that microbubbles can oscillate under the influence of ultrasound. At high intensities, this oscillation can lead to microbubble collapse and the production of mechanical forces on the clot surface, making the thrombus more susceptible to thrombolytics, thus accelerating thrombolysis.^5^

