### Design

The Microbubbles and UltraSound-accelerated Thrombolysis (MUST) trial is a single-arm phase II trial.

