### Primary study parameters

Main end points will be the safety and technical feasibility of the experimental treatment. Safety will be determined by treatment-related mortality, the occurrence of adverse events (AEs), serious adverse events (SAEs) and suspected unexpected serious adverse reactions (SUSARs). AEs will be defined as any undesirable experience occurring to a subject during the experimental treatment period, whether or not considered to be related to the investigational drug or intervention. SAEs will be defined as any untoward medical occurrence or effect that at any dose results in death; is life threatening (at the time of the event); requires hospitalisation or prolongation of existing in-patients’ hospitalisation; results in persistent or significant disability or incapacity; is a new event of the trial likely to affect the safety of the subjects, such as an unexpected outcome of an adverse reaction. SUSARs, which are related to the microbubble infusion and ultrasound application, are the formation of microemboli resulting in occlusion of the microcirculation, haemorrhages, hypotension, heart rhythm disorders and anaphylaxis. See the section ‘Adverse events’ for detailed handling procedures of AEs, SAEs and SUSARs. Haemorrhagic complications related to thrombolytic therapy will be reported according to the Standardized Bleeding Definitions for Cardiovascular Clinical Trials proposed by Mehran *et al*.^12^

Technical feasibility will be defined as accomplishment of the experimental protocol during the first hour of thrombolysis.

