### Adverse events

AEs will be recorded in detail in the electronic patient record. Any SAEs that occur after joining the trial will be reported to the accredited Medical Ethics Committee of our institution according to national and institutional guidelines. All AEs will be followed up until they have abated or until a stable situation has been reached. Depending on the event, follow-up may require additional tests or medical procedures as indicated and/or referral to a general physician or medical specialist. An interim analysis after 10 patients will be performed. If SAEs in these 10 patients have occurred, we will discuss the continuation of the study. The study will be prematurely terminated if two or more intracranial bleedings occur or more than five allergic reactions.

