### Statistical analysis

Categorised epidemiological/descriptive patient variables are summarised with frequencies and will be analysed with Fischer’s exact test or Pearson’s χ^2^ test. To avoid possible violations of the assumptions for parametric testing, such as a normal distribution pattern, we will employ non-parametric methods such as Spearman’s rank correlation and Mann-Whitney U test in the case of a skewed distribution or log transformation. For associations of two outcome measurements, we will use a correlation (Spearman’s rank) or single regression analysis. We will analyse the following outcomes by means of Kaplan-Meier curves: patency rate, amputation-free rate and intervention-free rate. We will assess heterogeneity in prognostic factors as a secondary analysis by means of χ^2^ tests. All tests will be performed two-sided, and p<0.05 will be considered to be statistically significant.

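### At 95% confidence, the stated rationale of confirming an SAE rate below 20% holds for 20 patients only if none has an SAE, and for 10 patients not at all

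*Protocol article*

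**What the plan says.** The rationale stands in the protocol article under Patients and eligibility criteria: "Usually, in a phase II trial 10–20 patients are investigated to confirm an occurrence of toxic effects or SAEs<20" (per cent). The next sentence applies it to this trial: "We chose a sample size of 20 to assess the safety of the investigational treatment". The section gives no confidence level, no expected SAE rate, no power and no acceptable number of events.

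Other places that bear on the point:

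- Design: "The Microbubbles and UltraSound-accelerated Thrombolysis (MUST) trial is a single-arm phase II trial".
- Statistical analysis: "All tests will be performed two-sided, and p<0.05 will be considered to be statistically significant". This is the only significance level in the article, and it is not tied to the sample size.
- Adverse events, on the look after 10 patients: "If SAEs in these 10 patients have occurred, we will discuss the continuation of the study".
- Adverse events, on stopping: "The study will be prematurely terminated if two or more intracranial bleedings occur or more than five allergic reactions". Neither this rule nor the interim look refers to an overall SAE rate or to 20%.
- Primary study parameters makes safety, with technical feasibility, the main end point. The Discussion makes a finding of safety and feasibility the condition for seeking funds for a randomised trial, and attaches no number to it.

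**The concern.** To confirm that a rate is below 20% is to exclude rates of 20% or more with stated confidence. Samples of 10 to 20 leave wide intervals for a proportion, so the statement needs checking at both ends of its range and for each plausible number of events.

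What is at stake is how the safety result is read. A trial with 1, 2 or 3 patients with an SAE would show 5%, 10% or 15%, all below 20%. A reader who relies on the stated rationale could take any of these as the confirmation for which the sample was chosen. Safety is a main end point and leads to the next trial, so that reading would carry weight.

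**Working it through.** **Inputs.** Threshold 20% and sample range 10–20 (Patients and eligibility criteria); n = 20 (same section); two-sided 5% level (Statistical analysis). The article gives no calculation behind n = 20, so there is no figure of its own to reproduce. The check asks whether the stated property holds.

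**Method.** Let x be the number of patients, out of n, with at least one SAE. The upper limit U of the exact (Clopper-Pearson) two-sided 95% interval solves P(X ≤ x | n, U) = 0.025. For x = 0 this reduces to U = 1 − 0.025^(1/n).

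**Ten patients, no events.** U = 1 − 0.025^(1/10) = 1 − 0.6915 = 30.8%. This is the best possible result with 10 patients, and it does not exclude 20%.

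**Twenty patients, no events.** U = 1 − 0.025^(1/20) = 1 − 0.8316 = 16.8%. This excludes 20%.

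**Twenty patients, one event.** Solve (1 − U)^20 + 20·U·(1 − U)^19 = 0.025, which gives U = 24.9%. This does not exclude 20%. Limits for two and three events follow in the same way.

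| Events / patients | Observed | Upper limit, two-sided 95% | Upper limit, one-sided 95% | P(this many or fewer) if true rate is 20% |
|---|---|---|---|---|
| 0/10 | 0% | 30.8% | 25.9% | 0.107 |
| 0/20 | 0% | 16.8% | 13.9% | 0.012 |
| 1/20 | 5% | 24.9% | 21.6% | 0.069 |
| 2/20 | 10% | 31.7% | 28.3% | 0.206 |
| 3/20 | 15% | 37.9% | 34.4% | 0.411 |

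**Smallest sample that can exclude 20%.** With no events, 1 − 0.025^(1/n) first falls below 0.20 at n = 17 (19.5%). At one-sided 95%, 1 − 0.05^(1/n) does so at n = 14 (19.3%). To allow one event takes 26 patients (two-sided) or 22 (one-sided). The lower part of the quoted range therefore cannot deliver the property at 95% confidence.

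**The lenient reading.** Suppose that confirming means only that the observed rate is below 20%, that is, at most 3 of 20. With a true rate of exactly 20%:

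P(X ≤ 3) = 0.8^20 + 20(0.2)(0.8^19) + 190(0.04)(0.8^18) + 1140(0.008)(0.8^17) = 0.0115 + 0.0576 + 0.1369 + 0.2054 = 0.411.

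A treatment at the threshold would pass 41% of the time, which is too often to be called confirmation.

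**Sensitivity to the method.** At two-sided 95% the other usual intervals agree. For 0/10 the Wilson, Agresti-Coull and Jeffreys limits are 27.8%, 32.1% and 21.7%; for 1/20 they are 23.6%, 25.4% and 21.1%. Only the Wald limit differs (0% and 14.6%), and it is not valid at such counts.

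**The case against.** **The sentence describes custom, not this trial's claim.** It says what is usually done in phase II, and the article then says that 20 were chosen to assess safety. A reader might infer that staying below 20% is the trial's main safety criterion, to be passed or failed. The article does not say so: no section makes 20% a decision rule, the stopping rules use other events, and the step to a randomised trial carries no number. No final analysis on 10 patients is planned either; that number is only the interim look. All of this stands and limits the point to the rationale. It does not rescue the rationale, because the article offers nothing else in support of 20.

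**No confidence level is given.** This also stands. At exact one-sided 90%, one event in 20 would be tolerated (18.1%), though 0/10 still fails (20.6%). At one-sided 95%, the Wilson limit (19.6%) or a mid-p value (0.040) would admit 1/20, and a Jeffreys limit would admit 0/10 (17.1%). The result must therefore be stated at two-sided 95%, the convention that the article itself sets.

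**The event counted.** The SAE definition is broad, including an event that "requires hospitalisation or prolongation of existing" inpatient stay, and the Introduction says of conventional thrombolysis that "such treatment is accompanied by a risk of major haemorrhagic complications, such as haemorrhagic stroke, in up to 8% of patients". A reader might infer that SAEs are the wrong event to count and that even a harmless addition would probably miss the mark. The article does not support that. It gives no overall SAE rate, the 8% is an upper figure, and this trial uses a low-dose regimen. Under assumed true rates of 2%, 5%, 8% and 10%, the chance of 0/20, (1 − p)^20, is 67%, 36%, 19% and 12%, so the answer depends on the assumption. Nor would counting only related SAEs be a clear gain. Primary study parameters ties haemorrhage both to the microbubbles and ultrasound and to the thrombolytic, and a single arm offers no control for attributing it.

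**Conclusion.** The stated rationale is wrong as written. At two-sided 95% confidence (exact binomial), 10 patients cannot exclude an SAE rate of 20% whatever the result, and 20 patients exclude it only with no event. With 1 to 3 events the data remain compatible with rates up to 24.9%, 31.7% and 37.9%.

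This rests on reading *confirm* at the article's general two-sided 5% level, on counting each patient once, and on all 20 being evaluable. At one-sided 90% one event would be tolerated. The point concerns a property that the article states and the design lacks; it does not show that 20 patients are too few for a feasibility and safety study, or that the trial applies a faulty decision rule.

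**What to change.** Keep 20 patients. Delete the rationale that 10–20 patients confirm a rate below 20%, and state the precision that the design has, for example:

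> With 20 patients the upper limit of the exact two-sided 95% confidence interval for the proportion with an SAE is 16.8% with 0 events, 24.9% with 1, 31.7% with 2 and 37.9% with 3; a rate of 20% or more is excluded only if no patient has an event.

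In the results, report the observed proportion of patients with an SAE together with this interval, and do not describe a rate below 20% as confirmed if any patient has an SAE. The SAE definition and the stopping rules need no change for this point.

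The cost is wording only, with no extra patients or data. The downside is that the stated safety property becomes less favourable.

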### Data handling

We will keep an electronic log of patients who fulfil the eligibility criteria, patients who are invited to participate in the study, patients recruited and patients who withdraw from the study. Reasons for non-recruitment will also be recorded. We will attempt to collect reasons for non-participation from patients who decline to take part. During the course of the study, we will document reasons for withdrawal from the study and loss to follow-up. Data will be stored electronically in Case Report Forms software with audit trail functionality and will be audited by the institutional Clinical Research Bureau. Only anonymised information will be stored and participants will only be identifiable by their unique study number, which will be kept in a separate file. Data will be securely stored on these servers for 15 years according to national guidelines. The principal investigator will have access to the final trial data set. No independent Data Management Committee was instated according to local ethics committee guidelines since the present study was not classified as a high-risk clinical study. This classification was approved by the local ethics committee based on the risk assessment form of the Netherlands Federation of University Medical Centres.

### Study procedures

#### Intervention

A flow chart of the patient work-up after presentation in our hospital is presented in figure 1. Low-dose thrombolytic treatment with urokinase (UK) will be initiated following our standard institutional protocol: a catheter is placed intra-arterially in the affected artery and a bolus injection of 500 000 International Units (IU) of UK (Medacinase Urokinase, Medac, Hamburg, Germany) will be followed by the continuous infusion of 50 000 IU of UK per hour and 9600 IU of heparin per 24 hours. The experimental treatment consists of (in addition to the standard thrombolytic therapy) the use of local 1.8 MHz transdermal ultrasound (Philips iE33 Ultrasound Machine, Eindhoven, the Netherlands), and the intravenous infusion of 4 Luminity phials (total 6 mL, diluted with saline 0.9% to 40 mL total, Lantheus MI UK, Newbury, Berkshire, UK) during the first hour of thrombolysis with U. An ACIST VueJect (Bracco Imaging Europe B.V., the Netherlands) infusion pump will be used to infuse the four phials continuously. Ultrasound will be intermittently activated (3 s manual flash to burst microbubbles with Mechanical Index (MI) 1.08 (pulse duration 20 μs, frequency 1.8 MHz, frame rate 39 Hz), 7 s of visualisation of inflow of the microbubbles at MI±0.11), at the site of occlusion during the first hour of thrombolysis. Criteria for discontinuation of the experimental treatment during the first hour will be the occurrence of any AEs potentially related to the experimental treatment, such as bleeding and allergic reactions.

**Figure 1 F1:**
[figure not shown]
Flow chart of patient work-up after presentation. ABI, Ankle Brachial Index; IU, International Units; MUST, Microbubbles and UltraSound-accelerated Thrombolysis; PCS, Pain Catastrophising Scale; QoL, quality of life; UK, urokinase; US, ultrasound; VAS, visual analogue scale.

### Assessments

#### Diagnostic measurements

Additional diagnostic measurements during admission including ECG, duplex ultrasound, angiography and microcirculation measurements (by Laser Doppler flowmetry) will be performed as depicted in figure 1.

A duplex ultrasound will be performed every 6±2 hours to monitor for signs of revascularisation. When resumption of flow is visualised by duplex ultrasound, angiography will be performed to confirm flow. Angiography will be performed at least once daily as standard procedure. Outside of routine hospital working hours, angiography will only be performed in emergencies as per standard care.

A standardised pain score (VAS, 1–10) and Pain Catastrophising Scale will be recorded every 3 hours by a nurse practitioner, research fellow or surgical resident to assess pain.

#### Fibrinogen monitoring

Following our standard institutional thrombolysis protocol, fibrinogen concentration will be checked during thrombolysis with the following criteria for treatment modification: if <1.0 g/L, the UK infusion rate will be lowered to 25 000 IU/hour; if <0.5 g/L, thrombolysis must be aborted temporarily and replaced by normal saline infusion. Three hours following treatment modifications, fibrinogen concentration will be re-evaluated and when>1.0 g/L thrombolysis will be restarted at an initial low-dose urokinase of 50 000 IU/hour.

### Postprocedural anticoagulation

After successful thrombolysis, the patient will be heparinised with low-molecular-weight heparin (fraxiparine) dosed based on body weight:<50 kg: two times a day 3800 IU (= 0.4 mL), 50–80 kg: two times a day 5700 IU (= 0.6 mL), >80 kg: two times a day 7600 IU (= 0.8 mL).

Concomitant therapy with coumarin derivatives will also be started at that time. Activated partial thromboplastin time will be measured daily during heparin treatment. The target range international normalised ratio will be 2.5–3.5; if this value is reached, heparinisation will be stopped and coumarin treatment will be continued.

